#### Outcome

Primary outcome measure is the children’s anxiety level, which will be measured with the Dutch version of the Spence Children’s Anxiety Scale (SCAS). The SCAS was developed to assess anxiety symptoms in children in the general population. The SCAS consists of six subscales, namely panic attack and agoraphobia, separation anxiety disorder, social phobia, physical injury fears, obsessive compulsive disorder and generalized anxiety disorder. The child version consist of 44 items on a *never* (0) to *always* (3) scale. The parent-report (P) version consist of 38 items in the scale on the same *never* (0) to *always* (3) scale. Six positive filler items of the children’s SCAS, were not included in the parent version. The items of the SCAS-P were formulated as closely as possible to the corresponding item of the child version of the SCAS. The SCAS shows high internal consistency, not only for the total scale, but also for each subscale
[23,28].

Secondary outcome measures will be active coping and positive cognitive restructuring, measured with the Dutch version of the Coping Strategies Checklist for Children (CSLK). This questionnaire is a children’s self-report measurement of coping skills, and consist of five subscales of which two subscales (active coping and positive cognitive restructuring) are included. The CSLK as used in this study consists of 24 statements which all start with “If I have a problem” followed, for example, by a statement such as “I tell others how I would like to solve it”. The children could choose between four reactions form *never* (1) to *always* (4). The CSLK shows high internal consistency
[29]. Cognitions about ones coping skills will be measured with the Dutch version of the Coping Questionnaire- Child (CQ-C)
[21], wherein children rated their ability to cope on a 7 point scale that ranged from *not at all able to help myself feel comfortable* (1) to *completely able to help myself feel comfortable* (7). The Self-efficacy Questionnaire for Children (SEQ-C) represents three domains of self-efficacy: social self-efficacy, academic self-efficacy and emotional self-efficacy. Only the latter is included in this study. The emotional self-efficacy scale consists of 8 items and pertains to the perceived capability of coping with negative emotions. Each item has to be scored on a 5-point scale with *not at all* (1) to *very well* (5)
[30].

Other outcomes are therapeutic alliance, measured with the Dutch translated version of the Therapeutic Alliance Scale for Children (TASC-nl). Wherein positive and negative aspects of the therapeutic alliance are measured. The TASC-nl includes 12 items on a 4-point scale, ranging from *not at all* (1) to *very much* (4). In previous research the TASC has demonstrated adequate internal consistency
[31]. Also anxiety symptoms in children are measured weekly by the Dutch version of the short Multidimensional Anxiety Scale for Children (MASC-10)
[32]. A 10-item self-report questionnaire, wherein items are rated on a 4-point scale ranging from *never true about me* (1) to *often true about me* (4). An overview of all measures at each time point is provided in Table 
1.

#### Statistical analysis

In accordance with the intent-to-treat principles, all children randomized to a condition will be included in the analyses to test the study hypotheses. Moreover, while randomization takes place within school level and children are ‘nested’ within these schools, we need to control for clustered data
[33]. Mplus is a statistical software program that has special features to deal with missing data and it allows analyzing complex data while considering their clustered structure. The 3-month follow up measurement of children’s anxiety levels will be used as the main outcome. Regression analyses will be conducted to test whether children in the experimental condition show a stronger decrease in anxiety symptoms at 3-months follow up compared to the control condition. The effect sizes as well as confidence intervals will be reported to determine both the magnitude and the effect of Coping Cat in the form of an indicative group-based prevention program. We are also interested in possible mediators in the relation between Coping Cat prevention program and anxiety levels. Using LGM in Mplus, we will test whether active coping, positive cognitive restructuring, and cognitions about ones coping ability function as mediators of treatment outcomes.

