## Methods/design

### Study design

Coping Cat will be adjusted and tested as an indicated CBT-based prevention program in Dutch primary school children, grades five through eight, with elevated levels of anxiety. This study is set up as a RCT with two conditions, with 130 children being randomly divided into the experimental (N=65) and control group (N=65). The experimental group will receive the adapted 12-session Coping Cat program. The control group will not receive a program. They will be offered the possibility to follow the program at the end of the study. Participating children and their mothers will complete baseline, post intervention, and a 3-month follow-up assessments (see Figure 
1). In addition, children in both experimental and control group will be asked to complete questionnaires weekly, just before every program session. All mothers who will complete all questionnaires will receive about 50 Euros for their participation. Children will receive few small for their participation.

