#### Randomization

Randomization will be applied within schools, with an equal number of experimental and control groups within one school. Children will be assigned to either the treatment or the control condition. Participants will be stratified by age (young: 7–9 years. & old: 10–12 years) and number (equally distributed over both conditions).

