#### Intervention condition

Children randomly selected to the intervention condition will receive a 12-session group program, each session lasting 1 hour. The sessions will take place every week, except for holidays. Groups consist of 7 to 9 children. The program will take place in schools after regular school hours. The program will start by using exercises enhancing group cohesion and safety. These exercises will continue throughout the program. In session 2 and 3, psycho-education about anxiety will be given and anxious feelings, both physical and emotional, will be addressed. Moreover, a relaxation exercise will be introduced. Children will be motivated to keep rehearsing relaxation every day during several weeks. The next step (session 4) will be to recognize thoughts and stimulate positive thinking. Meanwhile, exposure will be introduced beginning with session 4. Children will practice different anxiety provoking situations as homework at home, thus in low anxiety situation. In group therapy, children learn to make a plan when entering anxious situations (session 5). Beginning with session 6, children will experience anxious situation during therapy. They will start easy, being exposed to low-level anxiety situations as a group and slowly experiencing high-level anxiety situations that they will face alone. Meanwhile, children will repeat the techniques they acquired. Session 12 will end with an evaluation and little party to celebrate the children’s results. Parents will receive written information three times during the program, with specifics about the progress of their child and general information about the program.

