#### Trainers

Trainers (n=5) are child psychologists with ample experience in youth mental health care and knowledge of CBT. All trainers will participate in two-day training. In this training, the protocol will be explained and trainers will complete exercises and role-plays. Therapists will follow 2-h supervision sessions three times over the course of the program. A MA student in clinical child psychology will assist each therapist.

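### The primary analysis names school as its only clustering level, but the dependence that affects the treatment contrast lies in therapy groups found only in the experimental arm, within probably nine or fewer schools

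*Protocol article*

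**What the plan says.** The Statistical analysis section gives one reason for handling clustering: children are nested "within these schools, we need to control for clustered data". Mplus is named because it can take a clustered structure into account. The primary test is a regression comparing conditions on child anxiety at 3 months. No estimator, therapy-group term or reference distribution is given.

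Other sections describe the structure of the data:

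- Randomization: children are allocated within schools, "with an equal number of experimental and control groups within one school".
- Intervention condition: "Groups consist of 7 to 9 children", and "The program will take place in schools after regular school hours".
- Study design: 65 children per arm; "The control group will not receive a program".
- Trainers: five psychologists deliver the groups.
- Sample size calculation: the sample was enlarged for clustering, with no ICC, cluster size or design effect stated.

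The number of schools is not stated.

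**The concern.** Because both arms are present in every school, a shared school effect largely drops out of the difference between arms. What inflates the variance of that difference is correlation among children who attend the same 12 weekly sessions with the same trainer and peers. That correlation can arise only in the experimental arm, so the design is partially nested. The stated clustering level does not name it.

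The consequence depends on how school is handled. With school dummies or a school random intercept, group-level variation is treated as independent child-level error. With school-clustered robust errors, groups sit inside schools and their variation is captured, but the standard error then rests on few clusters. In either case the primary standard error can be too small, the confidence interval too narrow and the false-positive rate above its nominal level.

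**Working it through.** **The plan's own figure.** The 65 per arm can be neither reproduced nor refuted. For f² = .15 and an assumed two-sided alpha of 5%, the total needed is 55, 73 or 89 at 80%, 90% or 95% power with one tested predictor, and 68, 88 or 107 with two. Reaching 130 implies a design effect between 130/107 = 1.21 and 130/55 = 2.36. In any case, a larger sample protects power. It does not correct a standard error from a model that omits a source of correlation.

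**Number of groups and schools.** 65/9 = 7.2 and 65/7 = 9.3, so there are 8 or 9 experimental groups. With at least one experimental group per school and no group drawn from several schools, at most nine schools contribute. If each school ran two experimental groups, for example one per age stratum (which the article does not say), there would be about four.

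**Route 1: school dummies or random intercept.** Let m be the group size and ρ the therapy-group ICC, with equal total variance σ² and n children per arm. The experimental mean has variance (σ²/n)[1 + (m − 1)ρ] and the control mean σ²/n. The variance of the difference is therefore understated by the factor 1 + (m − 1)ρ/2. The approximate type I error is P(|Z| > 1.96/√factor). For m = 8:

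| Assumed ρ | Factor | Approximate type I error |
|---|---|---|
| 0 | 1.000 | 5.0% |
| .05 | 1 + 7(.05)/2 = 1.175 | 7.1% |
| .10 | 1 + 7(.10)/2 = 1.350 | 9.2% |
| .20 | 1 + 7(.20)/2 = 1.700 | 13.3% |

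Null simulations (4,000 trials per setting, school ICC 0 or .05, school fixed effects) agree:

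| Assumed ρ | Nine schools | Eight schools |
|---|---|---|
| 0 | 5.2-5.3% | 4.5-5.3% |
| .05 | 7.0% | 7.4-7.5% |
| .10 | 8.8-9.3% | 8.8-9.5% |
| .20 | 13.1-13.6% | 13.6-15.6% |

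A separate run of 6,000 trials with eight schools gave 4.9%, 7.2%, 9.5% and 14.3%. A school random intercept with a normal reference gave 7.3% at ρ = 0 and 10.5% at ρ = .10. That was only 400 trials, with a Monte Carlo standard error of about 1.5 percentage points.

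**Route 2: school-clustered robust errors with a normal reference.** With G schools of equal size, the uncorrected test rejects with probability P(|t(G−1)| > 1.96√((G−1)/G)). With the G/(G−1) correction this becomes P(|t(G−1)| > 1.96). No group ICC is needed.

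| Schools | Uncorrected | With G/(G−1) |
|---|---|---|
| 9 | 10.2% | 8.6% |
| 8 | 10.9% | 9.1% |
| 4 | 18.8% | 14.5% |

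Simulated rates for eight or nine schools lay between 8.3% and 11.6% across both versions. For four schools they lay between 13.9% and 19.6%.

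**Check of a remedy.** The corrected school-clustered error referred to t on (G − 1) degrees of freedom gave 4.6% to 5.9% in every simulated setting, at all group ICCs and with four, eight or nine schools.

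**The case against.** The strongest reply is that the article names no estimator. Its remark about Mplus and complex data fits school-clustered errors at least as well as school dummies, and those errors already absorb therapy-group correlation. What is then left is a choice of reference distribution, which a full analysis plan may settle and which a condensed article may properly leave out. This stands as far as it goes: under that reading the excess arises only with a normal reference, which the article does not state. It does not remove the point, because the only clustering rationale the article gives omits the level at which children are treated together, and two ordinary ways of following it are anti-conservative.

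Second, the size under Route 1 rests on an ICC that the documents do not give. At zero the fixed-effects test is nominal, and nothing in the documents supports or excludes .15 to .20 three months after the sessions end. This also stands, and is why a range is shown.

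Third, other readings exist. A model in which the condition effect varies by school would pick up group variance where each school has one experimental group, although the few-schools problem would remain.

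Fourth, the sample was enlarged for clustering. That may help power, but it does not bear on type I error.

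**Conclusion.** The point holds in conditional form. The stated clustering level is incomplete for a partially nested design, and the primary test is anti-conservative under either of two ordinary implementations:

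- School dummies or a random intercept, if the group ICC is above zero: for the dummies, about 7%, 9% and 13-14% at ICC .05, .10 and .20 (one simulated setting reached 15.6%).
- School-clustered errors with a normal reference: about 8-11% with eight or nine schools and 14-19% with four, whatever the ICC.

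The limit of about nine schools is an inference. It assumes 65 per arm, no group below seven and no group drawn from several schools.

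A reader might infer three stronger things that the documents do not support. One is that the two inflations add; they do not, since each belongs to a different way of handling school. Another is that the false-positive rate exceeds 5% in all circumstances; it does not at ICC 0 with school dummies, nor with a t reference on (schools − 1) degrees of freedom. The third is that trainer effects or the growth-model mediation analyses are shown to be invalid; neither was quantified. They call for caution only.

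**What to change.** Name the therapy group as a clustering level in the primary analysis, and state the estimator and reference distribution. Either of two routes would serve:

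(a) A partially nested model: school as a fixed effect, a therapy-group random effect in the experimental arm only, and small-sample degrees of freedom such as Kenward-Roger or Satterthwaite. This follows the design most directly, but its type I error was not simulated here, and it may need software other than Mplus.

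(b) School-clustered errors with a small-sample correction and a t reference on (schools − 1) degrees of freedom, which held about 5% in simulation.

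Report the therapy-group ICC in either case. Trainer can be examined as a sensitivity analysis, and school-clustered errors in the mediation models should be treated with caution given so few schools.

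The change is to analysis wording only; recruitment, treatment and data collection are untouched. The cost is wider confidence intervals. With nine groups of about 7.2 and an assumed ICC of .10, the variance of the effect is multiplied by 1 + 6.2(.10)/2 = 1.31, so the standard error rises by a factor of √1.31, about 1.15. For ICC .05 to .20 the variance factor runs from 1.16 to 1.62. The small-sample reference widens the interval further.

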### Aim and hypothesis

The main aim of this project is to conduct a Randomized Controlled Trial (RCT) to evaluate the effectiveness of a CBT based program called Coping Cat on the anxiety levels of Dutch primary school children. Therefore, Coping Cat will be revised and used as an indicative prevention group-based program. In this RCT, we will assign children to an experimental and a control group to test whether children who received Coping Cat as an indicated-group prevention program will have lower levels of anxiety at follow-up measurements. The second aim is to determine whether active coping, positive cognitive restructuring, self efficacy and coping cognitions operate as mediators. More specifically, we expect that a) anxiety levels of children in the prevention program will decrease significantly more over time compared to anxiety levels of children in the control group. b) Children who will follow the program will have significantly enhanced coping skills compared to the control group.

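### The primary analysis is worded both as a 3-month level and as a decrease, without saying how baseline SCAS enters; one baseline-adjusted model would settle it at no cost

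*Protocol article*

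**What the plan says.** The Statistical analysis section fixes the outcome as a level: "The 3-month follow up measurement of children’s anxiety levels will be used as the main outcome". The next sentence describes the test as one of change: "Regression analyses will be conducted to test whether children in the experimental condition show a stronger decrease in anxiety symptoms at 3-months follow up". The Aim and hypothesis section has the same pair of wordings: treated children "will have lower levels of anxiety at follow-up measurements", and their anxiety "will decrease significantly more over time compared to anxiety levels of children in the control group".

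Baseline data will exist. The Study design section says "Participating children and their mothers will complete baseline, post intervention, and a 3-month follow-up assessments", and Table 1 marks child SCAS at screening, baseline, post treatment and 3-month follow-up.

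On allocation, the Randomization section says "Randomization will be applied within schools, with an equal number of experimental and control groups within one school" and "Participants will be stratified by age", with two age bands. The Statistical analysis section links the school-level randomisation to a need to control for clustering. It does not mention the age bands. No covariate is named for the primary regression, and none is ruled out.

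**The concern.** The two sentences can be carried out in at least three ways: regress the 3-month score on condition alone, regress the change score on condition, or regress the 3-month score on condition with baseline as a covariate. The word decrease also leaves open which pre-treatment score is the reference, since child SCAS is taken at both screening and baseline. On one data set these analyses can give different estimates and p-values, so the primary result is not tied to a single model before the data are seen.

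The choice also affects precision. Taken literally, the first sentence points to follow-up only and the second to a change score, and both are less precise than baseline adjustment. That would matter if the true effect is near the .32 that the Sample size calculation section takes from earlier prevention research, where 65 per arm has little power to spare.

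**Working it through.** **Inputs from the article.** 65 children per condition; an effect of about .32 from the cited prevention research (metric not stated); a planning effect of f² = .15 (all from Sample size calculation).

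**Assumptions.** Two-sided α of .05; .32 read as a standardised mean difference d; equal SCAS variance at baseline and follow-up; no clustering and no dropout. The correlation r between baseline and 3-month SCAS within arm is not given, so it is taken from .3 to .7. Selecting children above a 1 SD screening cut-off may pull r down.

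**The plan's own figure.** The 65 per condition can be neither confirmed nor refuted, because α, power, number of predictors and intraclass correlation are not stated. For a single treatment term, f² = .15 needs 55, 73 or 89 children in total for 80%, 90% or 95% power. The stated 130 would then imply a clustering inflation of 130/55 = 2.36, 130/73 = 1.78 or 130/89 = 1.46. This does not bear on which regression is meant.

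**Variance of the treatment effect, relative to follow-up only.**
- Follow-up only: 1
- Change score: 2 − 2r
- Baseline-adjusted: 1 − r²

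The change score exceeds baseline adjustment by (2 − 2r) − (1 − r²) = (1 − r)², which is never negative. Follow-up only exceeds it by r². So for any r strictly between 0 and 1, adjustment is the most precise of the three. The change score is worse than ignoring baseline whenever r < .5.

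**Power at d = .32.** For follow-up only, d·√(n/2) = .32 × √32.5 = 1.824, and power is Φ(1.824 − 1.960) = 44.6% (44.1% with the t distribution). For the other two models, divide 1.824 by the square root of the relative variance.

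| r | Relative variance, change | Relative variance, adjusted | Power, follow-up only | Power, change | Power, adjusted | 65 per arm, adjusted, acts like |
|---|---|---|---|---|---|---|
| .3 | 1.40 | 0.91 | 44.6% | 33.8% | 48.1% | 71 |
| .5 | 1.00 | 0.75 | 44.6% | 44.6% | 55.8% | 87 |
| .7 | 0.60 | 0.51 | 44.6% | 65.4% | 72.4% | 127 |

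Example at r = .5: 1.824/√.75 = 2.106, and Φ(2.106 − 1.960) = 55.8%. The last column is 65/(1 − r²).

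**Power at the planning effect.** For two equal groups, f² = .15 corresponds to d = 2√.15 = .775. Power is 99.3% for follow-up only and at least 99.6% adjusted over the same range of r, a gain of under one percentage point.

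**The case against.** The strongest reply is that this is a condensed article. A covariate list is normally left to the full protocol or the analysis plan, and silence about baseline does not mean it is left out. A decrease cannot be tested without baseline, and a common reading of a 3-month outcome, a regression and a decrease taken together is follow-up regressed on condition with baseline as a covariate, which is the model recommended here. This stands as far as it goes: the article does not discard baseline, and a reader should not infer that it does. What remains is that the article words its primary test in two ways, and a literal reading of either gives a less precise analysis.

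A reader might also infer two competing estimands. The documents do not support that. Under randomisation expected baseline means are equal, so the difference in 3-month score and the difference in change have the same expectation. These are different estimators of one effect, and none is biased by the choice.

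A third tempting reading is that the analysis ignores the factors used in randomisation. School is explicitly handled as clustering; only the age stratum goes unmentioned. With 1:1 allocation, leaving out one balanced binary stratum typically makes standard errors somewhat too large, so invalid inference is not the worry.

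Finally, the power gain depends on an r that the documents do not give and on reading .32 as d. At the planning effect it all but vanishes, and an f² for a regression term may already be net of covariates. All of this is accepted. The ordering of the three variances, however, does not depend on the value of r between 0 and 1.

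**Conclusion.** The point holds in a limited form. The primary analysis is worded both as a level and as a decrease, the role of baseline SCAS is not stated, and the age stratum does not appear in the analysis. Baseline adjustment is more precise than either literal reading for any r strictly between 0 and 1 with equal variances.

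The size of the gain is conditional. If the effect is .32 on the d scale and r lies between .3 and .7, adjustment adds about 4 to 28 percentage points of power over follow-up only and about 7 to 14 over a change score, before clustering and dropout. If the effect is as large as f² = .15, the choice hardly affects power. Any shortfall at .32 is mainly a sample-size matter, which adjustment reduces but, over this range of r, does not remove. This is an improvement available at no cost. It is not evidence of a biased or invalid analysis.

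**What to change.** Replace the two sentences with one primary model: child SCAS total at 3 months regressed on condition, adjusted for baseline child SCAS as a continuous covariate and for age stratum, accounting for school as already planned. Take the reported effect size and confidence interval from the adjusted difference between conditions. Bring the hypothesis wording in Aim and hypothesis into line with it. Adding the screening SCAS as a further covariate is optional. Whether school is better handled as a covariate or through the planned clustering adjustment cannot be settled here, because the number of schools is not given.

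The cost is a sentence or two of text. Baseline SCAS is already in Table 1 and age band is already used for randomisation, so no new data, visits or children are needed. The wording should be fixed before outcome data are examined.

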### Data collection

Children will receive all questionnaires on paper and complete them at school, after school hours, in the presence of one of the researchers or trainers. This context is chosen deliberately to exclude any influence of parents. Mothers will complete the pre-, post-, and follow up measurement online. For this purpose, they will receive separate personal login codes that will give them access to their own questionnaire on a secured webpage. Mothers who prefer a paper questionnaire will be provided with a paper and pen version. Interference of the researcher will be diminished as much as possible by presenting the questionnaires digitally. Children and mothers are expected to complete the pre-, post-, and follow up assessments within 45 minutes. The weekly measurements will take about 10 minutes to fill out. Non-responding mothers and absent children will be contacted by phone and motivated to complete the questionnaire on paper or directly by phone. An overview of all measures at each time point is provided in Table 
1.

**Table 1 T1:** Overview of measures

**Measure**	**Screening**	**Baseline**		**Weakly**		**Post treatment**		**3 month follow up**	
	**Child**	**Child**	**Mother**	**Child**	**Therapist**	**Child**	**Mother**	**Child**	**Mother**
Spence Children's Anxiety Scale (SCAS)	X	X	X			X	X	X	X
Multidimensional Anxiety Scale for Children (MASC- 10)		X		X		X		X	
Suicidal item Child Depression Inventory (CDI)		X				X		X	
Coping Strategies For Children^1^ (CSLK)		X		X		X		X	
The Self-Efficacy Questionnaire for Children^2^ (SEQ-C)		X		X		X		X	
Coping Questionnaire Child (CQ-C)		X		X		X		X	
Therapeutic Alliance Scale for Children (TASC)				Session 1/6/12	X				
Demographic characteristics		X	X						
5 most anxious situations (for treatment purposes)		X							

^1^ Subscales used: Active coping & Positive cognitive restructuring.

^2^ Subscale used: Emotional self efficacy.

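### The mediation test most naturally uses child reports for both coping and anxiety; if reported coping differs by arm, same-informant variance can pass for mediation, and the mother-rated SCAS has no stated role as a check

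*Protocol article*

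**What the plan says.** The protocol article states the mediation analysis in one sentence of its Statistical analysis section: a growth model in Mplus is to test whether the two coping strategies (active coping and positive restructuring) and "cognitions about ones coping ability function as mediators of treatment outcomes". Self-efficacy, the fourth mediator in the aims, is not in that sentence.

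The mediators come from the child. The Outcome section says of the coping checklist: "This questionnaire is a children’s self-report measurement of coping skills". Of the coping-cognitions questionnaire it says "wherein children rated their ability to cope on a 7 point scale". Table 1 marks both, and the self-efficacy questionnaire, in child columns only: at baseline, weekly, post treatment and 3 months.

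For the outcome, the Statistical analysis section says: "The 3-month follow up measurement of children’s anxiety levels will be used as the main outcome". The Outcome section says: "Primary outcome measure is the children’s anxiety level, which will be measured with the Dutch version of the Spence Children’s Anxiety Scale (SCAS", and then describes both a child and a parent version. Neither sentence names the informant. Child report is the natural reading, because the Abstract ties the main outcome to the child's own symptom level and eligibility is screened on the child's SCAS.

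A second informant is available. Under Data collection, "Mothers will complete the pre-, post-, and follow up measurement online", and Table 1 marks the mother's SCAS at baseline, post treatment and 3 months. The Statistical analysis section gives it no stated role. The Strengths and limitations section does not mention same-informant bias.

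**The concern.** Mediation needs two links: the program changes coping, and coping changes anxiety. Random allocation supports only the first. The second is an association between two sets of answers that, on the natural reading, come from the same child.

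Several features make a shared reporting component plausible here. Controls receive no program, so children know their arm. The program teaches positive thinking and coping. Forms are filled in with a researcher or trainer present. The coping-cognitions scale asks how far the child can make himself or herself feel comfortable, which lies close to low anxiety. A child who answers more favourably on a given day will look better on both scales without any causal link.

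What is at stake is the trial's second aim, the mechanism conclusion. The main test of effectiveness does not depend on this point.

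**Working it through.** The article gives no figure for the mediation test, so there is none to reproduce. From the document: 65 children per arm, 130 in all. Assumed, because the document does not give them: two-sided alpha of 0.05, the program's effect d on reported coping (in SD), and the partial correlation r between reported coping and reported anxiety given arm that comes only from the shared informant. The true effect of coping on anxiety is set to zero.

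**Step 1. Analytic check.** Mediation is declared when both paths are significant, and the two rejection probabilities are multiplied.

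- Program-to-coping path: noncentrality = d × √(65/2), df 128. For d = 0.5 this is 2.85, power 0.81. For d = 0.32 it is 1.82, power 0.44. For d = 0 the rejection rate is 0.05.
- Coping-to-anxiety path: noncentrality = r × √127 / √(1 − r²), df 127. For r = .1, .2, .3 this is 1.13, 2.30, 3.54, with rejection 0.20, 0.63, 0.94.

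| Gain in reported coping | r = .1 | r = .2 | r = .3 |
|---|---|---|---|
| d = 0.5 | 16% | 51% | 76% |
| d = 0.32 | 9% | 28% | 41% |
| d = 0 | 1% | 3% | 5% |

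The spurious indirect effect is d × r. At d = 0.5 it is 0.05, 0.10 or 0.15 SD.

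**Step 2. Simulation with baseline adjustment.** Each scenario used 2,000 simulated trials of 65 per arm with a true mediator effect of zero. Both the mediator and the outcome model were adjusted for baseline. This two-wave regression stands in for the growth model, with mediator and outcome taken on the same occasion. School clustering was not simulated, and the simulated mother rating carries no reporting bias.

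| Scenario | Child outcome | Mother outcome |
|---|---|---|
| No arm difference in reported coping; shared share 20–30% | 4–5% | under 1% |
| Gain 0.5 SD; occasion-specific share 10% / 20% / 30% | 34% / 79% / 86% | about 4% |
| Gain 0.32 SD; occasion-specific share 20% | 44% | 2% |
| Gain 0.5 SD; stable reporting style only, share 20% / 30% | 8% / 12% | 5% |
| No real gain; program shifts reporting by 0.5 / 1 SD of the bias, share 20% | 26% / 69% | 2% / 4% |

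Without baseline adjustment, the stable-style scenarios gave 51% and 74%. Adjustment therefore removes most of the stable style. It does not remove bias specific to the occasion, or a shift caused by the program.

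**The case against.** **Tempting stronger readings.** A reader might infer that the plan specifies a child-rated mediation outcome. It does not: the informant is left open, and child report is an inference, though a strong one. A reader might also infer that shared-reporter variance is enough by itself to create a mechanism. Both steps above show otherwise: without an arm difference in reported coping, the rate stays at or below 5%.

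**Planned model and timing.** The article plans a growth model with mediators measured weekly and an outcome 3 months after the program. Growth modelling deals with most stable reporting style, and bias specific to one program week is not shared with a 3-month SCAS. This objection largely stands. It leaves two routes: modelling coping and anxiety from the same occasion, which Table 1 allows but the analysis text does not state, or a reporting shift that lasts. The percentages are therefore conditional illustrations and not predictions for the planned model.

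**A condensed article.** Cross-informant sensitivity analyses are often left to an analysis plan, which is not shown here. That is why the point is a recommendation and not a claim of contradiction. Still, the article does state the mediation model for a declared aim, and two informants' SCAS scores would fit its wording.

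**The mother is not a clean comparator.** This stands. Mothers are unblinded, and under Intervention condition parents receive written information on their child's progress during the program. Mothers may also be less sensitive to internal anxiety. Requiring agreement between informants could reject a true mechanism.

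**Limited consequence.** The Discussion already says that more research is needed before working elements can be clearly identified. That tempers the stakes, but it does not tell the reader about same-informant bias.

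**Conclusion.** The concern holds in a conditional form. All mediators are child-reported, the mediation outcome is most naturally the child SCAS, and a mother-rated SCAS collected at all three main assessments has no stated role in the test. If reported coping differs by arm, through a real gain (which the article's own hypothesis expects) or through a treatment-induced shift in reporting, same-occasion shared variance or a lasting shift can inflate the coping-to-anxiety path and be read as mediation.

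With d = 0.5 and no true mediator effect, the false-mediation rate is 16%, 51% or 76% at r = .1, .2 or .3. It is near or below nominal when reported coping does not differ by arm. The values of d and r and the variance shares are assumptions, and the analytic figures lie outside the planned growth model. The point affects what can be concluded about mechanism and leaves the main effectiveness comparison untouched.

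**What to change.** In the Statistical analysis section, name the child SCAS as the outcome of the main mediation model. Add one prespecified sensitivity analysis that repeats the model with the mother-rated SCAS at 3 months, adjusted for the mother's baseline SCAS and the baseline mediator. Report both indirect effects with confidence intervals. Describe a mediation effect seen only with the child-rated outcome as possibly reflecting same-informant bias, and list that bias among the limitations. Do not make agreement with the mother model a condition for reporting a mechanism.

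The cost is one repeated model per mediator on data already scheduled. The drawbacks should be stated with the result: lower precision, some missing mother data, possibly lower sensitivity to internal anxiety, and unblinded mothers who in the program arm receive written progress information.
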